### Data management

The procedures reported in the study regarding the conduct, development, and documentation have been prepared to ensure compliance with the ethical principles set out in the Declaration of Helsinki and its revisions. The research design also took into account the directives provided by the General Data Protection Regulation (GDPR, Regulation (EU) 2016/679) (76). The study will be conducted by taking into account the regulatory requirements and the legal obligations and will be launched following the assessment and approval of the study by an independent Ethics Committee and the completion of the administrative obligations required by the institution where the study is carried out. Furthermore:

before enrollment, all participants must receive complete information on the study.to be enrolled, it will be necessary that the participants or their legal guardians give consent to the processing of personal data in anonymous and aggregate form, under the General Data Protection Regulation (GDPR 2018, Regulation (EU) 2016/679) on the protection of individuals and respect for the processing of personal data (76).the participant must be informed that his data can be reviewed by authorized personnel or by members of the relevant ethics committee and by officials of the competent regulatory authorities.the participant is also informed and asked to provide informed consent for data retention for up to 15 years from the conclusion of the study.

The processing of personal data and information will take place in compliance with current privacy legislation. All data will be digitized, made anonymous, and archived on a centralized and secure IT platform. They will be marked with a numerical code and will not contain the name of the participant in the study or data that can identify him. The data will be archived in databases of the IRCCS INRCA of Ancona and will be kept for 15 years beyond the end of the study.

### Data analysis

An analysis plan will be defined on the basis of which the analyzes themselves will then be conducted. Data entry will be carried out using special software, providing blocks and data entry checks to reduce the number of entry errors. The quality of the data and their internal consistency will be evaluated using Cronbach's Alpha and other specific tests. The questionnaires will first be checked manually to check the completeness of the compilation and any obvious inconsistencies. Automated routines will then be used to detect outliers and dubious records. In such cases, the necessary data cleaning will be carried out.

The first step of the analysis will be exploratory. The descriptive analysis of the sample will be conducted through the classic techniques of uni- and bi-variate statistical analysis. The categorical variables will be summarized by reporting the absolute and relative frequencies, while for the continuous variables the mean and standard deviation or median and interquartile deviation will be reported depending on the distribution (evaluated through the Shapiro–Wilk test). Significant differences between outcomes and exposures will be compared using the Chi-square test or the Fisher's exact (in the case of categorical variables) or the *T*-test or the Mann-Whitney test (in the case of comparisons of continuous variables between groups depending on the distribution of the same). To check for any distortions due to non-responses during the survey, the characteristics of the subjects in the sample will be compared with those of the non-respondents.

In a second step, the follow-up data analysis will be conducted to evaluate the effectiveness of the J-DOME intervention. This phase of analysis will involve the use of multivariate statistics, in particular, the variance analysis models for repeated measures to identify the factors associated with the variation of the main secondary clinical end-points.

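### Step one lets the observed distribution choose between a t-test and Mann-Whitney for outcomes, and step two does not clearly name MMSE and ADAS-Cog, so their deciding between-arm analysis is not fixed

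*Protocol article*

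**What the plan says.** The Data analysis section sets out two steps.

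- **Step one.** "The first step of the analysis will be exploratory". For continuous variables, the summary statistic (mean with SD, or median with interquartile deviation) is chosen "depending on the distribution (evaluated through the Shapiro–Wilk test". The next sentence turns to testing: "Significant differences between outcomes and exposures will be compared using the Chi-square test or the Fisher's exact" for categorical variables, and the t-test or Mann-Whitney "in the case of comparisons of continuous variables between groups depending on the distribution of the same". The objects compared are outcomes and exposures, so the tests are not confined to baseline characteristics. No covariate is named, and the text does not say whether follow-up scores or changes are compared.
- **Step two.** "In a second step, the follow-up data analysis will be conducted to evaluate the effectiveness of the J-DOME intervention". The method is analysis of variance for repeated measures, and its stated purpose is "to identify the factors associated with the variation of the main secondary clinical end-points".

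Elsewhere, the Trial design section and Table 2 make MMSE and ADAS-Cog primary. The Sample size section takes changes in MMSE and ADAS as the main outcomes and sizes both on a repeated-measures ANOVA with two groups and two assessments. Table 3 schedules MMSE, ADAS-Cog and all the secondary scales at T0, T1 and T2.

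**The concern.** A t-test compares means, and Mann-Whitney compares ranks. If the observed distribution picks the test, the quantity reported as the between-arm effect is known only once the data are seen, and it can differ between scales or visits for reasons unrelated to treatment.

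In a step that is clearly descriptive this would matter little. Here, however, step one tests outcomes for significance, while the step-two sentence names secondary endpoints only. Within the analysis section, neither sentence clearly assigns MMSE and ADAS-Cog to one deciding between-arm comparison. At stake are a fixed effect measure for the primary outcomes and the precision available from the T0 score, which is collected anyway.

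**Working it through.** **1. The plan's own figures.** Inputs from the Sample size section: effect sizes 0.47 (MMSE) and 0.35 (ADAS), 90% power, significance level 0.05, 2 groups, 2 assessments. The within-person correlation is not given; 0.5 is assumed. For the between-groups effect, with the stated values read as Cohen's f:

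λ = N f² m / (1 + (m − 1)ρ), df 1 and N − 2, m = 2.

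- MMSE: N = 38 gives λ = 38 × 0.2209 × 2 / 1.5 = 11.19 and power 90.2%; N = 36 gives 88.6%. The stated 38 is reproduced.
- ADAS: N = 68 gives λ = 68 × 0.1225 × 2 / 1.5 = 11.11 and power 90.7%; N = 66 gives 89.9%. The stated 68 is reproduced.
- Dropout: 68 × 1.15 = 78.2, the stated 78.

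So the trial was sized on a repeated-measures ANOVA for the primary outcomes. The step-two wording does not carry this over.

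**2. Does the switch inflate type I error?** Simulation: 34 per arm, 3,000 trials per setting, no treatment effect, Shapiro-Wilk at 5% in each arm, and Mann-Whitney if either arm rejects.

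| Data | Sent to Mann-Whitney | Type I error of the two-stage rule |
|---|---|---|
| Normal | about 10% | 4.9% and 5.5% |
| Log-normal, σ = 0.5 | about 95% | 4.8% and 5.2% |

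The two type I figures are for T0–T1 correlations of 0.5 and 0.7. The 10% agrees with 1 − 0.95² = 9.75%. Error stays at about 5%; what changes with the data is the effect measure.

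**3. What would one baseline-adjusted model gain?** Assumptions: 33 per arm (39 × 0.85 = 33.15); 0.47 and 0.35 treated as SD differences at T1 (step 1 reproduces the sample sizes by reading them as Cohen's f, so this is for illustration only); equal SDs at T0 and T1; two-sided 5%. Effective SD of each analysis, relative to the outcome SD:

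- follow-up score only: 1
- change score (equivalent to group-by-time with two visits): √(2(1 − ρ))
- linear model with T0 as covariate: √(1 − ρ²)

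Noncentrality = (d / SD) × √(33/2). Example, d = 0.47 and ρ = 0.7: change score 0.47 / 0.775 × 4.062 = 2.46, power 68%; adjusted 0.47 / 0.714 × 4.062 = 2.67, power 75%.

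| Effect | Assumed ρ | Follow-up score only | Change score | T0 as covariate |
|---|---|---|---|---|
| 0.47 SD | 0.5 | 47% | 47% | 58% |
| 0.47 SD | 0.7 | 47% | 68% | 75% |
| 0.47 SD | 0.8 | 47% | 84% | 88% |
| 0.35 SD | 0.5 | 29% | 29% | 37% |
| 0.35 SD | 0.7 | 29% | 44% | 50% |
| 0.35 SD | 0.8 | 29% | 60% | 65% |

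The fair comparison is with the change-score column, because the effectiveness model already contains T0. The gain there is 4 to 11 percentage points (84% to 88%; 47% to 58%).

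**The case against.** The strongest reply is that the plan assigns the treatment effect elsewhere. Step one is called exploratory, effectiveness is a separate second step, and the Sample size section puts MMSE and ADAS on a repeated-measures ANOVA, which includes T0. The phrase about secondary endpoints may be a slip for main and secondary. An analysis plan is also promised, and details of covariates and test hierarchy normally belong there.

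Much of this stands, and it rules out several stronger conclusions that a reader might infer:

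- *That the pre-test decides the trial's treatment effect.* The text does not say so. Even the link from Shapiro-Wilk to the test is an inference: the Shapiro-Wilk clause governs the summary statistic, and the test sentence refers only to the distribution. It is a reasonable inference, since no other check is named.
- *That each outcome has two routes to significance and hence an inflated error rate.* This would treat an exploratory test as a second confirmatory one, which the document nowhere does.
- *That MMSE would usually change test between T0 and T1.* This depends on assuming whole-number scores. The Mini-mental state examination section says the reported score is corrected for age and education, and on near-continuous scores Shapiro-Wilk rejects far less often at T0.
- *That the baseline is thrown away.* The t-test or Mann-Whitney might be run on changes, and the ANOVA contains T0. The follow-up-only column above is therefore not the power of the effectiveness analysis.

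What remains is that the published text tests outcomes with a method chosen by the data, does not say those tests are non-decisive, and words the effectiveness model for secondary endpoints only. That is a matter of what the text states, so the promised analysis plan does not remove it.

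**Conclusion.** The point holds in a limited form and is minor. The effect measure for step-one outcome comparisons depends on the observed distribution, and the deciding between-arm analysis for MMSE and ADAS-Cog is not clearly fixed, because the step-two wording does not match the Sample size section. The switching rule itself does no visible harm to type I error (4.8% to 5.5% in simulation).

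The measurable benefit of the correction is precision. Against a change-score test, power rises by 4 to 11 points for 0.47 SD and by 5 to 8 points for 0.35 SD, over assumed T0–T1 correlations of 0.5 to 0.8. These gains rest on 33 per arm and on reading the effect sizes as SD differences. The correlation is not in the document.

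**What to change.** 1. State that step-one comparisons are descriptive and will not be used to judge effectiveness.
2. For MMSE, ADAS-Cog and each secondary scale, name one between-arm analysis that applies whatever a normality test shows: a linear model of the T1 (and T2) score on arm and T0 score, reporting the mean difference with its 95% confidence interval. Add a rank-based or bootstrap version as a sensitivity analysis for scales that may be skewed, such as NPI and CSDD.
3. Correct the step-two sentence so that it covers the primary outcomes as well as the secondary ones.

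The cost is wording in the protocol and the promised analysis plan. No visit, measurement or participant is added, since T0 is already collected for every scale. The linear model would replace the repeated-measures ANOVA as the deciding analysis, so the plan should say so before outcome data are examined by arm.

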## Methods and analysis

### Trial design

The study is designed as a single-blinded (outcome assessors) randomized controlled trial to test the effectiveness of a training program that combines the jDome virtual reality system for aerobic exercise with computerized cognitive training *via* tablet. The Experimental Group (EG) will receive computerized cognitive training with the Brainer web platform and aerobic training with the jDome system. The Control Group (CG), on the other hand, will receive computerized cognitive training with the Brainer web platform and aerobic training with a standard exercise bike.

Assessment will be performed at the baseline (T0), at the end of intervention (after 8 weeks-T1), and 3 months after the end of intervention (follow-up T2).

The primary aim is to assess the stabilization of the global cognition of people with mild-stage Alzheimer's disease at the Mini-Mental State Examination (MMSE) and at the Alzheimer's Disease Assessment Scale-Cognitive Subscale (ADAS-Cog).

The secondary aim is the analysis of the modification of the quality of life, mood, behavioral disturbances, and physical function in people with mild-stage Alzheimer's disease.

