### Sample size

The sample size estimation for this study was carried out considering the changes in MMSE score and ADAS for the cases compared to controls as the main outcomes. In the study by Han et al. (53), 64 subjects with MCI or mild dementia were enrolled to take part in combined cognitive training, cognitive stimulation, reality orientation, physical therapy, reminiscence therapy, and music therapy. The scores of the MMSE and the ADAS significantly improved in the experimental group compared to the control group with the following effect sizes: 0.47 for MMSE and 0.35 for ADAS. Assuming the same effect sizes in a repeated measures ANOVA model (2 groups and 2 repeated assessments), setting the statistical power at 90% and a significance level equal to 0.05, the expected sample size should be 38 to capture an effect on the MMSE and 68 subjects for ADAS. Considering a 1:1 ratio between cases and controls and a potential dropout rate of 15%, the overall sample size should be 78 subjects (39 cases and 39 controls).

It is hypothesized that this sample dimension is more than sufficient to grasp a variation also for secondary outcomes for which a treatment effect size is assumed of a similar or higher entity than that identified for the primary outcome.

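### The only efficacy sentence aims the repeated measures ANOVA at factors linked to secondary end-points, states no between-group contrast for MMSE or ADAS-Cog, and names a method less efficient than a baseline-adjusted model

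*Protocol article*

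**What the plan says.** The Data analysis section describes two steps.

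- **Step one.** "The first step of the analysis will be exploratory". It contains descriptive summaries and bivariate tests: "Significant differences between outcomes and exposures will be compared using the Chi-square test" or Fisher's exact test for categorical variables, and a t-test or Mann-Whitney test for continuous ones.
- **Step two.** Its purpose is that "the follow-up data analysis will be conducted to evaluate the effectiveness of the J-DOME intervention". The only model named for it is repeated measures analysis of variance, and the task given to that model is "the variance analysis models for repeated measures to identify the factors associated with the variation of the main secondary clinical end-points".

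The section also announces that "An analysis plan will be defined". On non-response it says that "the characteristics of the subjects in the sample will be compared with those of the non-respondents".

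Elsewhere in the article, Trial design states the aim: "The primary aim is to assess the stabilization of the global cognition", measured by MMSE and ADAS-Cog. Table 2 lists these two scales as primary. The Sample size section is built by "considering the changes in MMSE score and ADAS for the cases compared to controls as the main outcomes", in a repeated measures ANOVA with 2 groups and 2 assessments. Assessments are planned at T0, T1 (8 weeks) and T2 (3 months after the end of the intervention).

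**The concern.** The efficacy sentence should say which outcomes are tested, which contrast answers the trial question, and how that contrast is estimated. This one names secondary end-points where the primary ones belong. It describes a search for associated factors where a randomised comparison belongs. It gives no group or group-by-time contrast, and does not say which of the two post-baseline visits it concerns. An analysis plan that follows it inherits the mismatch, and one that departs from it contradicts the published protocol. An unclear primary contrast also leaves room to settle outcome, contrast and visit after the data are known.

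The second issue is efficiency. In a trial of 78 people with a T0 score already collected on every outcome, a repeated measures ANOVA makes weaker use of that score than a model that adjusts for it.

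**Working it through.** **1. Passages side by side**

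| Place in the article | Outcomes | Contrast |
|---|---|---|
| Trial design | MMSE, ADAS-Cog (primary) | Stabilisation; no comparison worded |
| Table 2 | MMSE, ADAS-Cog (primary) | Not applicable |
| Sample size | MMSE, ADAS | Change, cases against controls |
| Data analysis, step two | 'Main secondary' end-points | Factors associated with variation |

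The last row disagrees with the other three on outcomes, and with Sample size on the contrast.

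**2. The article's own sample size figure**

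Inputs from Sample size: effect sizes 0.47 (MMSE) and 0.35 (ADAS), 2 groups, m = 2 assessments, power 90%, alpha 0.05. Assumed, because they are not stated: the effect sizes are Cohen's f, and the correlation rho between assessments is 0.5.

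For the group main effect, the noncentrality is lambda = N f² m / (1 + (m − 1) rho), with 1 and N − 2 degrees of freedom.

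- MMSE: 38 × 0.2209 × 2 / 1.5 = 11.19, power 90.2%
- ADAS: 68 × 0.1225 × 2 / 1.5 = 11.11, power 90.7%

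These match the stated 38 and 68, and 68 × 1.15 = 78.2 gives the stated 78. For the group-by-time interaction, lambda = N f² m / (1 − rho), and the same inputs need only 16 and 24. So the stated figures correspond to a group effect averaged over both assessments, while the text of that section speaks of change. The section ties repeated measures ANOVA to MMSE and ADAS but does not settle the contrast, which is why both sections need to be aligned.

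**3. Efficiency of the named method**

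Take one follow-up, with equal SD s at T0 and follow-up and correlation rho. The group-by-time test of a two-visit repeated measures ANOVA is the test of the difference in mean change.

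- Variance of a change score: 2 s² (1 − rho)
- Residual variance after adjusting for T0: s² (1 − rho²)
- Ratio: (1 − rho²) / (2(1 − rho)) = (1 + rho) / 2

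| rho (assumed) | Adjusted / change-score variance | Excess variance of change score |
|---|---|---|
| 0.3 | 0.65 | 1/0.65 − 1 = 54% |
| 0.5 | 0.75 | 1/0.75 − 1 = 33% |
| 0.7 | 0.85 | 1/0.85 − 1 = 18% |
| 0.8 | 0.90 | 1/0.90 − 1 = 11% |

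If the SDs differ (s0 at T0, s1 at follow-up), the change-score variance is s0² + s1² − 2 rho s0 s1 = (s0 − rho s1)² + s1² (1 − rho²). This is never below the adjusted variance, and equals it only when s0 = rho s1. The direction therefore holds generally, but the size depends on inputs that the article does not give. The MMSE entry floor (above 19) could narrow the T0 spread and shrink the gain for that scale.

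**The case against.** The strongest reply is context. The sentence just before the quoted one says that the step evaluates effectiveness. Sample size attaches a two-group repeated measures ANOVA to MMSE and ADAS and calls them the main outcomes, so 'main secondary' may well be 'main and secondary' with a word dropped. Step one also compares outcomes between groups. All of this is fair, and it defeats the inference a reader might draw that the trial would produce no primary result. The documents show that such an analysis is intended. What remains is that the sentence fixing the model does not say so. Restoring the dropped word would still leave the aim as a search for factors, with no contrast. Step one is labelled exploratory and cannot stand in for the primary test.

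A reader might also infer that a complete-case analysis has been fixed. It has not. Repeated measures ANOVA in its classical form drops anyone missing a visit, but the article states no such rule, its wording does not exclude a mixed model, and missing-data handling may sit in the plan still to be defined.

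Nor does the text support saying that 12 of 78 participants would be discarded. That figure (78 × 0.15 = 11.7) is the whole planned dropout, already allowed for in the sample size. A model of T1 and T2 outcomes recovers only those with partial follow-up; it cannot recover people lost before T1, and the article gives no split.

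Finally, a group-by-time test is valid under randomisation. Baseline adjustment is a gain in precision and does not correct a bias.

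**Conclusion.** The point holds in two parts. First, the only efficacy sentence conflicts with Trial design, Table 2 and Sample size on which outcomes the model serves, and it states no between-group contrast. This is a misstatement in the text and rests on no assumption. Leaving detail to a later plan does not excuse it, because the sentence is not silent.

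Second, the named ANOVA is less efficient than a baseline-adjusted model. For a single follow-up the variance ratio is 0.65 to 0.90 over an assumed rho of 0.3 to 0.8, with equal SDs at the two visits. With both T1 and T2 in the model, that ratio describes each visit's contrast, not an overall test.

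No power figure should be attached. The article states neither rho nor whether 0.47 and 0.35 are Cohen's f or d, and the choice matters: read as d (f = d/2), the main-effect calculation with rho 0.5 would need 146 and 260 instead of 38 and 68.

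**What to change.** Replace the efficacy sentence with wording to this effect: for MMSE and ADAS-Cog (primary), and then for each secondary outcome, the difference between the experimental and control groups at T1 and at T2 will be estimated in participants as randomised, adjusted for the T0 score and using all available T1 and T2 data, and reported with a 95% CI. A mixed model for repeated measures is one suitable choice. State separately that any search for factors associated with change is exploratory. Reconcile this with Sample size, so that both sections name the same outcomes, contrast and assessments.

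The cost is a few lines of text and slightly more modelling work. No visits, measurements or participants are added.

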## Discussion

The aim of the present study is to evaluate a treatment protocol for patients with mild Alzheimer's disease aimed at improving firstly cognitive performance, and secondly mood, quality of life, and physical performance. The treatment in question involves two different moments, first, the cognitive training performed using a Brainer platform and second, the aerobic physical activity performed using an exercise bike. Finally, the treatment also uses virtual reality to offer the person a reminiscence activity *via* the jDome system by having him or her ride a bicycle along roads known and important to him or her.

We focus on patients with mild Alzheimer's disease to test whether exercise combined with cognitive training and reminiscence therapy can actually lead to benefits in terms of increased cognitive plasticity and hippocampal neurogenesis. To study the effectiveness of the treatment, we will divide the population into an experimental group, treated with cognitive therapy and physical activity with the jDome system, and a control group, treated instead with cognitive therapy and physical activity with a simple exercise bike. During the virtual course, the person's memories will be stimulated so as to increase motivation for the activity and use and thus train the cognitive functions. With the intervention of a psychologist during the session, cognitive stimulation will also be expanded to other functions, such as attention, language, visuospatial skills, and spatial orientation.

Another important aspect of the protocol is the check of the results obtained not only at the end of the treatment but also after 3 months from the end of the treatment to verify the maintenance and generalization of the results gained.

